### Eligibility criteria {10}

The inclusion and exclusion criteria are listed in Table 1 below. Children aged ≥6 months to < 10 years of age who report sleeping in selected study clusters > 90% of the nights of each month and do not have any plans to travel outside the study area will be eligible for inclusion in the study. Children who have a measured hemoglobin at baseline screening/enrollment, re-screening/re-enrollment for intervention phase of < 7 g/dL, or with known chronic disease or who have signs of clinical decompensation will also be excluded from the study. During follow-up of enrolled subjects, study clinicians will have the option to conduct a Hb test for enrolled subjects when they may present signs of anemia to see if they might need additional treatment beyond malaria ACTs (if malaria infection is indicated).

**Table 1 Tab1:** Inclusion and exclusion study criteria

Inclusion criteria	Exclusion criteria
Children ≥ 6 months to < 10 years of age	Children ≤ 6 months to > 10 years of age
Children with Hb ≥ 7 g/dL and no other serious illness	Children with Hb < 7 g/dL with signs of known chronic disease or other serious illness, or Hb < 6 g/dL with signs of clinical decompensation
Sleeps in cluster > 90% of nights during any given month	Sleeps in cluster < 90% of nights during any given month
Not participating in another clinical trial investigating a vaccine, drug, medical device, or a medical procedure during the trial	Participating or planned participation in another clinical trial investigating a vaccine, drug, medical device, or a medical procedure during the trial
Provision of informed consent form (ICF) signed by the parent(s) or guardian	No provision of ICF signed by the parent(s) or guardian

Persons who are participating in another clinical trial investigating a drug, vaccine, medical device, or procedure will also be excluded from the study. The written consent of the parent or legal guardian of each child will be required for inclusion in the study.

For those participants fitting the study criteria, trained study personnel will be employed to ensure the timely distribution, application, and replacement of the SR products and to perform periodic, unannounced spot checks to confirm the SR product is properly installed.

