### Who will take informed consent? {26a}

The study will be explained and the consent form read in the local language to the head of HH or spouse (for SR or placebo application in the home) or to the parent/guardian of children eligible to participate in the cohort. The study will be explained in local dialect and time allowed for questions to be answered. Once all concerns are addressed, ICFs written in French (the official language in Mali) will be signed or a thumbprint taken (either on paper or electronically).

Informed consent will take place with two study populations. The study will be conducted at the cluster scale (first population) and all HHs within the selected clusters will be eligible to receive the SR product (second population). Therefore, all heads of HHs in the selected clusters will be approached and be read an ICF. Before being asked to sign the ICF, they will be asked to confirm their understanding of the ICF, to have the SR product placed in their houses and replaced every 4 weeks. The ICF will also ask that they report to the study clinic if they experience any adverse events (AEs) or serious adverse events (SAEs) of interest. AEs and SAEs of interest will be described verbally and will be provided in written form. Secondly, a cohort of children will be enrolled to estimate the impact of the SR product on the incidence of malaria disease (SR and placebo clusters). Parents/guardians of eligible children selected to participate in the cohort will be asked to provide consent. An attempt to obtain written, informed consent from both parents of the child will be made, but consent from only one parent will be required for participation (national protocols will be observed).

Separately, parent(s) and guardian(s) of eligible children aged ≥ 6 months to < 10 years will be asked to provide consent to participate in the baseline cohort with a 6 -month duration and the follow-up cohort with a 24-month duration. Children aged between ≥ 6 months and < 10 years old in identified HHs will be approached by the study team, to explain the study and ask them to voluntarily participate in the study. If subjects consent to participate, the study team will screen eligible children. After screening children for eligibility, the eligible children will then be tested and treated for malaria free of charge during the course of the study.

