### Outcomes {12}

The primary outcome measure of this cRCT will be the number of first-time malaria infections (*Plasmodium falciparum* (Pf)) during the intervention period (24 months) as measured by microscopy in children aged between 6 months and 10 years.

Secondary outcome measures include:
2.Number of overall new *Plasmodium falciparum* malaria infections during the intervention period (24 months) as measured by microscopy in children aged between 6 months and 10 years;3.Number of first-time *Plasmodium falciparum* malaria infections during the intervention period (24 months) by two age groups (≤ 6–59 months old; 5–10 years old) as measured by microscopy in children aged between 6 months and 10 years;4.Number of overall *Plasmodium falciparum* malaria infections during the intervention period (24 months) by two age groups (≤ 6–59 months old; 5 years to 10 years old) as measured by microscopy in children aged between 6 months and 10 years;5.Anopheline-human contact (indoor and outdoor) using human biting rate (HBR) as an indicator for all anophelines and by anopheline species as measured by human landing catch (HLC) during 12-h intervals on a quarterly basis during the intervention period (24 months);6.Anopheline parity rate as an indicator of population age structure for all anophelines and by anopheline species as measured by mosquito ovarian dissections from a sub-sample of anophelines collected during HLC procedures during the intervention period (24 months);7.Anopheline infectivity using sporozoite rate as an indicator for all anophelines and by anopheline species as measured by laboratory detection of sporozoites in mosquito head-preps from a sub-sample of anophelines collected during HLC and/or CDC-light trap procedures during intervention period (24 months);8.Anopheline infectivity using entomological inoculation rate (EIR) during the intervention period (24 months) as an indicator for all anophelines and by anopheline species as measured by calculating the number of sporozoite-infected anopheline mosquitoes captured per person during intervention period from HLC and/or CDC-light trap procedures;9.CDC-light trap indoor density for all anophelines and by anopheline species as measured by CDC-light trap collections during 12-h intervals on a monthly basis during the intervention period (24 months);10.Insecticide resistance as measured by WHO filter paper test and CDC bottle assays during the baseline (6 months) and intervention period (24 months);11.Adverse events (AEs) and serious adverse events (SAEs) as measured by solicited and unsolicited reports during baseline (6 months) and intervention period (24 months). Mean, minimum and maximum frequency, and percentage of AEs and SAEs across clusters among enrolled subjects will be summarized by the treatment arm.

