### Implementation {16c}

Intervention distribution will occur after the completion of baseline phase analyses has been completed and underlying assumptions on study power (incidence, CV) are verified. All consented HHs will have the product placed inside their homes at the manufacturer’s recommended application rate of 2 units per 9 m^2^ floor area. Trained study staff will be responsible for the management of product implementation which will include the initial deployment of product, subsequent removal, and replacement at 4-week intervals.

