## Data collection and management

### Plans for assessment and collection of outcomes {18a}

#### Mapping of the study area and baseline census measurements

Prior to enrollment, structures in the study area will be mapped using GPS coordinates and assigned a unique HIN. A baseline questionnaire will be administered during mapping to measure housing structure and HH demographic characteristics. Profiles of enrolled houses that could potentially confound effect on mosquitoes will be generated. Profiles will include house construction, socioeconomic status, number of inhabitants and their age, current HH vector control method(s) including ITNs.

Villages will be considered as the unit of randomization. According to Mali’s 2009 National Population Census [20], the circle of Kolondieba is comprised of 11 rural communes with a population size of 201,456 inhabitants. This population is divided between 30,079 HHs and 14,730 family compounds, where a compound is defined as a family unit with one or more structures. A typical family compound has 5 HH members.

Clusters will be randomly allocated to intervention or placebo using standard statistical software. All HHs in each village will be invited to participate in the study by allowing study staff to place SR or placebos in their HH. SR or placebo will be placed in each HH that consents. Within each cluster, individual compounds will be enumerated and then randomly selected for inclusion in each cohort.

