### Adverse event reporting and harms {22}

The SR product contains transfluthrin, a chemical used in currently available HH mosquito control products such as mosquito coils. Exposure to the product may cause mild eye and skin irritation, however, these effects are typically transient and disappear after time. The product may be harmful if chewed on or swallowed, so HH owners will be advised to keep it away from children. The SR product will be fixed at a position out of the reach of children and will be monitored at replacement to ensure it has not been moved. If a product is found to have been removed from its position in the HH, study staff will discuss with the HH owner to determine why it was removed and if there was any problem that led to its removal. Study staff will also reiterate safety precautions that should be taken in regard to the SR product.

AEs and SAEs of interest will be collected through passive surveillance by CHVs on cohort participants and other HH members receiving the study product. Additionally, AE and SAEs of interest will be solicited from study participants during follow-up visits (every 2 weeks) either in the house or clinic. We will also rely on passive surveillance of the outpatient registers at the local health facilities for reports of AE/SAE. Additionally, we may collect unsolicited reports during compound visits and/or product replacement. Anyone experiencing the SAEs or AEs of interest will be encouraged to seek care at the study clinic where clinical staff will attend to them at no cost.

An AE includes any noxious, pathological, or unintended change in anatomical, physiological, or metabolic functions as indicated by physical signs, symptoms, and/or laboratory detected changes occurring in any phase of the clinical study whether associated with the study intervention or placebo. This definition includes an exacerbation of pre-existing conditions or events, intercurrent illnesses. A SAE is any untoward medical occurrence that results in death, is life-threatening, results in persistent or significant disability/incapacity, requires in-patient hospitalization or prolongation of existing hospitalization, or is a congenital anomaly/birth defect in the offspring of a study subject. In addition, important medical events that may jeopardize the participant or may require intervention to prevent one of the other outcomes listed above will be considered serious.

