AEs and SAEs will be reported in future publications. Harms will be coded in accordance with MedDRA at time of safety outcome reporting. Summaries of symptom-based AEs, SAEs, and death reports observed during the studies will be reviewed by the trial DSMB at predetermined checks (quarterly). The AE/SAE will be labeled “Probable,” “Possible,” “Plausible,” or “Unlikely” due to SR. Summary statistics of AEs/SAEs, including mean, minimum, and maximum frequencies and percentages across clusters among enrolled subjects, will be provided by the treatment arm. Statistical comparisons of the AE/SAE rates between the two arms will be conducted upon the completion of the study. Two sets of statistical analyses will be run. One set will compare the proportion of having at least one occurrence in each symptom-based AE/SAE during the whole study between the two arms, and the other will compare the total number of occurrences for each AE/SAE between the two study arms. If the data collected permits meaningful statistical hypothesis testing, p-values from the treatment comparisons will be reported, with multiplicity correction via the FDR approach [21].

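### Product goes into every consenting household and adverse events are collected from all its members, but the stated end-of-trial safety summary covers only enrolled subjects

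*Protocol article*

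**What the plan says.** **Exposure.** The Implementation section states: "All consented HHs will have the product placed inside their homes at the manufacturer’s recommended application rate". The section on mapping and baseline census measurements agrees: "SR or placebo will be placed in each HH that consents". The informed consent section likewise makes every household in the selected clusters eligible for product. None of the three sets an age or health limit on residents.

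**Cohort.** Under Eligibility criteria the cohort is restricted: "Children aged ≥6 months to < 10 years of age who report sleeping in selected study clusters" may enter, subject to haemoglobin and illness exclusions. The consent and cohort-enrolment sections enrol one child per household.

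**Collection.** Under Adverse event reporting and harms, adverse events (AEs) and serious adverse events (SAEs) of interest "will be collected through passive surveillance by CHVs on cohort participants and other HH members receiving the study product". Outpatient registers and unsolicited reports at compound visits or product replacement add to this. Study participants are also asked about events every 2 weeks.

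**Reporting.** Item 11 under Outcomes says that the "percentage of AEs and SAEs across clusters among enrolled subjects will be summarized by the treatment arm". The harms section repeats the restriction: "Summary statistics of AEs/SAEs, including mean, minimum, and maximum frequencies and percentages across clusters among enrolled subjects, will be provided by the treatment arm". It then announces statistical comparisons of event rates between arms at the end of the study, without naming the population.

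**Oversight.** The DSMB reviews AEs, SAEs and deaths quarterly, including a comparison of rates between arms. That review is not limited to enrolled subjects.

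**The concern.** The population from which events are collected is wider than the population for which they are to be summarised. Adults, siblings, infants under 6 months and children screened out for illness or low haemoglobin live with the emanator and fall under surveillance. The stated safety outcome by arm does not include them.

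This matters because the results go to the WHO Vector Control Advisory Group as evidence on a product meant for whole households, and the harms section itself warns of harm if the product is chewed or swallowed. A published safety conclusion based only on the screened cohort would say nothing about an imbalance in serious events or deaths among the other residents, although reports of those events would be in hand.

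**Working it through.** **Which population each passage names**

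| Step | Population named | Section |
|---|---|---|
| Product placement | All consenting households | Consent; Implementation; Mapping |
| Event collection | Cohort children and other household members | Harms |
| Quarterly DSMB review, by arm | Not restricted | Data monitoring committee; Harms |
| Safety outcome, item 11 | Enrolled subjects | Outcomes |
| Descriptive summary by arm | Enrolled subjects | Harms |
| Final comparison between arms | Not stated | Harms |

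**The plan's own cohort figure**

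- Baseline enrolment: 60 clusters × 32 = 1,920, as the Abstract states.
- After randomization: 60 × 26 = 1,560 children, 780 per arm. The figure of 26 comes from the Sample size section.

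**Size of the exposed population**

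The documents do not give the cluster populations. Assume that each cluster is one average village of the district. The mapping section gives 201,456 inhabitants and 30,079 households (2009 census), and Study setting gives 161 villages.

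- Residents per village: 201,456 / 161 = 1,251. Households per village: 30,079 / 161 = 187.
- 60 average villages: 60 × 201,456 / 161 = about 75,100 residents, and 60 × 30,079 / 161 = about 11,200 households.

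Cohort as a share of exposed residents = 1,560 / (75,077 × consent proportion):

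| Household consent (assumed) | Share |
|---|---|
| 100% | 2.1% |
| 50% | 4.2% |
| 25% | 8.3% |

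**Within cohort households only**

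- Residents per household: 201,456 / 30,079 = 6.7.
- One enrolled child is 1 / 6.7 = about 15% of residents, or 20% if a household has 5 members.

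This second share does not depend on the village-size or consent assumptions.

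**What the cohort alone can exclude**

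If no event of a given type is seen among 780 children in the active arm, the 95% upper bound is about 3 / 780 = 0.38%. This ignores clustering and loss to follow-up.

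**Which breakdowns are feasible**

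- *Infants under 6 months.* The census precedes enrolment, which began on July 8, 2021. Trial status dates the end of baseline by January 15, 2022, and product follows baseline. An infant counted in the census is therefore at least 6 months old at deployment. Infants under 6 months during the 24 intervention months are not in the census, so it gives no denominator for them.
- *Anaemic residents.* Haemoglobin is measured at cohort screening. The section on enrolment to receive the product says that no routine blood samples are sought there. This group cannot be identified outside the cohort.

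**The case against.** A reader might infer that events in non-cohort residents are gathered and then ignored. The documents do not support that. The DSMB compares event rates by arm each quarter with no limit to the cohort. The harms section promises to report AEs and SAEs in publications without restricting whom they concern. The final comparison leaves its population open. Only outcome item 11 and the descriptive summary are tied to enrolled subjects.

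The term itself is not watertight. One section is headed as enrolment to receive the product, and others speak of enrolled households. Cohort children remain the likelier meaning of enrolled subjects, since the eligibility and cohort follow-up sections use the phrase that way. Eligibility criteria also links product distribution to participants who meet the study criteria. That sits badly with placement in all consenting households and should be reconciled.

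The restriction also has a sound reason. Cohort children are asked about events every 2 weeks and have a known denominator. Other residents are followed mainly passively, and percentages across clusters need a denominator. This justifies keeping the cohort as the main safety set and not pooling the two sources. It does not justify having no end-of-trial table for the wider source.

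**Conclusion.** The mismatch stands in a limited form. Product and event collection cover all members of consenting households, while the stated safety outcome and summary by arm cover, on the natural reading, one child per household. The gap is in the end-of-trial reporting and in the unstated population of the final comparison. It is not a gap in safety oversight.

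The cohort is about 2% to 8% of exposed residents, given average-sized villages, 2009 census figures and 100% down to 25% consent. Within cohort households it is about 15%. These are head-count shares. They do not measure lost safety information, because reports from the other residents are less complete. It is also tempting to ask for rates in young infants or in anaemic residents, but the data described cannot supply them.

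This is an inexpensive improvement to the published safety conclusion. It does not affect the efficacy analysis.

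**What to change.** In Outcomes item 11 and in Adverse event reporting and harms:

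1. Keep the cohort summary as the actively solicited safety set, and name the cohort as the population for the final comparison between arms.
2. Add a separate table by arm of AEs of interest, SAEs and deaths reported among other residents of households that received product. Do not pool it with the cohort.
3. Give counts by arm and cluster, with approximate rates per household or per resident where the mapping data supply a denominator.
4. Show events in infants under 6 months as counts only, and attempt no breakdown by anaemia.

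The cost is one more set of tables from reports already collected. The downside is that ascertainment in these residents is mainly passive and less complete, so the table must be labelled descriptive.

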### Trial design {8}

The study design is a cluster randomized control double-blinded clinical trial with 30 clusters per treatment arm (SR intervention and placebo), with a 6-month baseline follow-up period, and a post cluster randomization follow-up period of 24 months with intervention. For the evaluation of the primary objective, 26 subjects (HHs) are required within each cluster factoring in a 35% loss-to-follow-up (LTFU) rate. It is expected that 80% of the baseline subjects (HHs) will continue to participate in the intervention period therefore a total of 32 subjects (HHs) will be enrolled at the start of baseline. At least one child aged from ≥ 6 months to < 10 years of age from each HH will be recruited for malaria follow-up during each baseline and intervention trial periods.

Twenty clusters (10 SR, 10 placebo) will be randomly selected to estimate the impact of the SR intervention on entomological measures of malaria transmission using CDC light traps. From these 20 clusters, a subset of 12 clusters (6 SR, 6 placebo) will be randomly selected for HLC. Light trap collections will be conducted in 10 randomly selected houses every month to assess the impact of the SR intervention on the indoor density of *Anopheles* mosquitoes. Indoor HLC will be conducted in four randomly selected houses within each of the subset 12 clusters every quarter. Four houses will be randomly selected at the start baseline, for a total of 48 sentinel houses). These 48 houses will remain fixed throughout the trial period.

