#### Cohort follow-up

All efforts to overlay commencement of baseline follow-up with start of malaria transmission season will occur; however, programmatic timelines may not allow for perfect alignment. The primary goal during baseline will be to ensure capturing incidence across a range of anticipated transmission timing in order to inform on sample size assumptions prior to intervention.

At enrollment, children will be cleared of parasitemia with a treatment dose of ACT, just after deployment of the study product. This will be done so incidence of malaria parasitemia following study product deployment can be measured. The distribution of the SR will occur after the completion of the baseline period. At this time, cohort participants will be presumptively cleared of parasites with a treatment dose of AL unless they have recently been treated (within the last 2 weeks). This will be done so incidence of malaria infection following study product deployment can be measured.

During the entire study period, each subject will be asked to come to the nearest study health facility for a total of 30 scheduled clinic follow-up visits for passive malaria case detection. Scheduled clinic visits will occur one time per month during each the 6-month baseline period and 24-month period with intervention. Subjects will be visited at their home if they cannot reach the clinic for the scheduled follow-up. In addition, each subject will have scheduled HH visits conducted by study staff for active malaria case detection where blood sampling will occur only for those subjects reporting fever history. Scheduled HH visits will occur one time per month during each the 6-month baseline period and 24-month period with intervention. Lastly, subjects will be informed to make an unscheduled clinic visit any time during the trial should they experience malaria-related symptoms.

At each visit, the parent/guardian will be asked about the recent use of ITNs and other vector control interventions as well as the recent history of the child’s illness, recent travels outside the HH, and recent use of anti-malarial drugs. At every other visit (on a monthly basis), a blood sample will be taken for malaria RDT, and a blood smear for confirming malaria diagnosis. At the intervening visits, a blood sample will only be taken if the child has a recent history of fever. Total blood volume for samples at each visit will not exceed 500 μl.

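### The between-arm AE/SAE comparison has no post-installation window and, read with the outcome definition, counts six pre-product months that dilute any harm signal

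*Protocol article*

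**What the plan says.** The section Adverse event reporting and harms {22} plans two end-of-study comparisons. The first is of proportions: "One set will compare the proportion of having at least one occurrence in each symptom-based AE/SAE during the whole study between the two arms". The second compares the total number of occurrences of each AE/SAE and states no time window. P-values are to be reported, with a false discovery rate correction, if the data allow meaningful testing.

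Outcome 11 in Outcomes {12} sets the period for this endpoint: "Adverse events (AEs) and serious adverse events (SAEs) as measured by solicited and unsolicited reports during baseline (6 months) and intervention period (24 months". The same item adds that the "percentage of AEs and SAEs across clusters among enrolled subjects will be summarized by the treatment arm", with no split by period. The harms section defines an AE as a change "occurring in any phase of the clinical study whether associated with the study intervention or placebo".

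Cohort follow-up states that "The distribution of the SR will occur after the completion of the baseline period". Trial design {8} places the 24 months with intervention after cluster randomization. So no child has an arm or a product during baseline.

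The wording is not uniform. When coding malaria and other acute illness as AEs, the harms section treats the study as lasting 24 months. Sample size {14} and the data sharing policy speak of a two-year study.

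**The concern.** A between-arm safety comparison should count events that the product could have caused. Events before installation arise in the same way in both arms and carry no information about the product. Pooling them with later events pulls the contrast toward no difference, which is the wrong direction of error when the question is harm.

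For at least one occurrence the effect is mechanical. A child with one rash or runny nose during baseline already counts as positive, and nothing after installation can change that. The loss is therefore greatest for common symptoms, and the harms section lists skin irritation and runny nose among the effects considered possible with this product.

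**Working it through.** **1. Which window does the text support?**

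- For including baseline: outcome 11 names both periods. Outcomes 1 to 9 in the same list are limited to the intervention period, so adding baseline for AEs looks deliberate. The AE definition covers any phase. Cohort follow-up counts the entire study period as 30 scheduled monthly clinic visits, which reproduces as 6 + 24 = 30.
- For the intervention period only: the 24-month and two-year phrases noted above.
- No sentence limits "during the whole study between the two arms" to time after installation.

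Baseline share of follow-up for a child present in both periods: 6/30 = 20%.

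**2. Total occurrences.** Assume a constant monthly event rate, multiplied by RR only in the 24 product months. The rate ratio over 30 months is (6 + 24 × RR)/30.

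| True RR | 30-month ratio |
|---|---|
| 1.25 | (6 + 30)/30 = 1.20 |
| 1.5 | (6 + 36)/30 = 1.40 |
| 2.0 | (6 + 48)/30 = 1.80 |

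One fifth of the excess is lost. The expected absolute difference in counts does not change; the ratio shrinks and unrelated variation is added.

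Baseline began in July 2021, and the setting section gives a malaria peak from July to November, so the baseline rate may differ from the later average. If it is m times that average, the ratio is (6m + 24 × RR)/(6m + 24). For RR 1.5 this gives 1.44, 1.40, 1.33 and 1.29 at m = 0.5, 1, 2 and 3.

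**3. At least one occurrence.** With monthly risk p on placebo and p′ on product, the 24-month difference is (1 − p)^24 − (1 − p′)^24. Adding baseline multiplies both terms by (1 − p)^6, so the difference is multiplied by (1 − p)^6.

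| Assumed p | Multiplier |
|---|---|
| 1% | 0.94 |
| 2% | 0.89 |
| 5% | 0.74 |
| 10% | 0.53 |

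Example with p = 2%, doubled by the product. Over 24 months: 1 − 0.98^24 = 38.4% against 1 − 0.96^24 = 62.5%, a difference of 24.0 points before rounding and a ratio of 1.63. Over 30 months the difference is 24.0 × 0.89 = 21.3 points and the ratio 1.47.

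**4. Power.** Inputs: 26 × 30 = 780 children per arm from Sample size {14}. Assumed: two-sided 5% test, exponential event times, all children contributing both periods in full, design effect 1 or 2.

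| Rate per month, RR | Design effect | 24 months | 30 months |
|---|---|---|---|
| 0.005, 1.5 | 1 | 84% | 76% |
| 0.005, 1.5 | 2 | 55% | 47% |
| 0.10, 1.25 | 1 | 89% | 64% |
| 0.10, 1.25 | 2 | 61% | 37% |

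**The case against.** The strongest reply is that outcome 11 says when events are collected, not that the periods are pooled. Outcome 10 (insecticide resistance) carries the same two-period window, and its analysis is split into baseline and each intervention year. Arms exist only after allocation, and part of the harms section speaks of 24 months. This stands in part: the window is inconsistent, and a reader should not infer that pooling is settled beyond doubt. But no such split is written for AEs, and nothing confines the test to exposed time.

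A second reply is that the exact safety window belongs in the SAP. That would hold if the article were silent. It states a window, and the stated one gives the worse comparison.

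Two stronger readings are tempting and are not supported.

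- A reader might infer that this is the only between-arm safety evidence. It is not: under {21a} the DSMB compares AE and SAE rates by arm every quarter. It is the only planned end-of-study inferential comparison.
- Trial design {8} says "It is expected that 80% of the baseline subjects (HHs) will continue to participate in the intervention period", so a reader might infer that the remaining baseline children enter the arm denominators without ever receiving product. The document does not say this. Consent is separate for the two phases, children are re-screened and re-enrolled for the intervention, and product is offered to all consenting households in a cluster.

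**Conclusion.** The concern holds as a stated but inconsistent safety window. If outcome 11 is followed, both planned comparisons are diluted toward no difference. The direction is certain whenever the product raises event rates. The size is moderate and rests on assumed rates, because the document gives none: one fifth of the excess rate ratio under a constant rate, and a risk difference cut by about 11% at 2% per month and about 47% at 10%. A large effect, such as a doubling at 2% per month, would still be plain. The practical loss is for modest increases in common symptoms. If the 24-month reading was intended, the analysis is sound and only the wording needs correcting.

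**What to change.** In Adverse event reporting and harms {22} and in outcome 11, state that both between-arm AE/SAE comparisons use events with onset on or after first product installation in the household, among children enrolled for the intervention phase. Tabulate baseline AEs separately by later allocation as a balance check, or use them as a covariate. Reconcile outcome 11 with the 24-month and whole-study wording in the harms section so that one safety window is named.

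The cost is about one sentence in each place. Recording at installation and at each replacement is already planned, and AEs are already collected at visits every two weeks, so no new data are needed. The only statistical downside is slightly fewer events in the comparison, and those removed say nothing about the product.
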